## Abstract

**Background:**

Fusion of lumbar spine segments is a well-established therapy for many pathologies. The procedure changes the biomechanics of the spine. Initial clinical benefits may be outweighed by ensuing damage to the adjacent segments. Various surgical devices and techniques have been developed to prevent this deterioration. "Topping off" systems combine rigid fusion with a flexible pedicle screw system to prevent adjacent segment disease (ASD). To date, there is no convincing evidence that these devices provide any patient benefits.

**Methods/Design:**

The study is designed as a randomized, therapy-controlled trial in a clinical care setting at a university hospital. Patients presenting to the outpatient clinic with degenerative disc disease or spondylolisthesis will be assessed against study inclusion and exclusion criteria. After randomization, the control group will undergo conventional fusion. The intervention group will undergo fusion with a supplemental flexible pedicle screw system to protect the adjacent segment ("topping off").

Follow-up examination will take place immediately after treatment during hospital stay, after 6 weeks, and then after 6, 12, 24 and 36 months. Subsequently, ongoing assessments will be performed annually.

Outcome measurements will include quality of life and pain assessments using questionnaires (SF-36™, ODI, COMI). In addition, clinical and radiologic ASD, work-related disability, and duration of work disability will be assessed. Inpatient and 6-month mortality, surgery-related data (e.g., intraoperative complications, blood loss, length of incision, surgical duration), postoperative complications, adverse events, and serious adverse events will be documented and monitored throughout the study. Cost-effectiveness analysis will also be provided.

**Discussion:**

New hybrid systems might improve the outcome of lumbar spine fusion. To date, there is no convincing published data on effectiveness or safety of these topping off systems. High quality data is required to evaluate the benefits and drawbacks of topping off devices. If only because these devices are quite expensive compared to conventional fusion implants, nonessential use should be avoided. In fact, these high costs necessitate efforts by health care providers to evaluate the effects of these implants. Randomized clinical trials are highly recommended to evaluate the benefits or harm to the patient.

**Trial Registration:**

ClinicalTrials.gov: NCT01224379

## Background

Some controversy remains regarding fusion procedures of the lumbar spine. There is evidence that lumbar spine fusion is more efficient than common nonsurgical treatment [1]. On the other hand, more recent research suggests that primary spinal fusion might not be more beneficial than intensive rehabilitation [2]. Nonetheless, fusion is a well-established surgical treatment for various pathologies of the lumbar spine, and is frequently used for patients with chronic low back pain.

Spinal fusion changes the biomechanics of the spine, e.g., by creating increased motion in the segments adjacent to the fused level. Initial clinical benefits from fusion might be outweighed by the adjacent segment disease (ASD) that ensues. It is important to distinguish between adjacent segment degeneration, which is a radiological term and does not lead to clinical symptoms, and adjacent segment disease. Adjacent segment disease is the clinical presence of symptoms that correlates to degenerative disease seen radiographically adjacent to the index level [3].

As a result, disc arthroplasty and dynamic stabilization techniques have evolved with the hope that the technology can prevent this degeneration [4]. One of the most rapidly evolving techniques in spinal surgery is posterior dynamic stabilization (PDS). Over the past few years, the industry has developed various types of flexible pedicle screw systems, including the "topping off" technique (a rigid system with an attached flexible system for the adjacent segment). Other surgeons perform procedures including a monosegmental rigid fusion plus an interspinous spacer superiorly [5]. To simplify the discussion of PDS devices, Khoueir et al. [6] classified them into:

1. Interspinous spacer devices,

2. Pedicle screw/rod-based devices, and

3. Total facet replacement systems.

The concept is to maintain or restore intervertebral motion in a controlled fashion, whether by restricting extremes of spinal movement or by dampening the kinetic energy involved in motion. The goal of these implantable devices is to mimic the behavior of the healthy spinal column [6,7]. Companies have developed various types of flexible pedicle screw systems (e.g. Surgicraft's Graf ligament, Bioflex's Spring rod, Dynesys^®^, AccuFlex™, Medtronic's Peek rod, Isobar^®^) and topping off systems (e.g. DTO™, DSS™, CosmicMIA™). Topping off has been reported to provide dynamic stabilization along with a consequent reduction of degeneration in the adjacent segment [8,9]. Maserati et al. performed a retrospective analysis of a population after undergoing the topping off procedure. They concluded it was a promising alternative for multilevel fusion with the potential to avert ASD [10]. However, in a recently published, prospective, randomized clinical trial of 60 patients comparing fusion with a hybrid system device versus conventional fusion over 6 years of follow-up, clinical results did not differ between the groups (ODI, VAS, satisfaction). Although the hybrid fixation showed less progression of degeneration in the adjacent segment, there was a higher rate of implant failure. This study group did not recommend prophylactic dynamic stabilization [11]. Overall, to date there is no convincing evidence that these systems provide any clinical benefit whatsoever.

It is not even clear whether the adjacent degeneration visible radiographically is important for clinical outcome. Fusion of spinal motor segments leads to increased forces acting on adjacent levels and can result in ASD. Adjacent instability is reported even 6 to 12 months post-surgery [4,12]. Average rates vary. In a retrospective study, Cheh et al. identified radiographic ASD in 42.6% of patients (average follow up 7.8 years). Oswestry scores were worse in patients with radiographic ASD. Clinical ASD developed in 43% [4]. Other authors have reported incidence of ASD up to 24% (average follow up 39 months). In that study, instability developed more frequently superior to the fusion [12]. Yang et al. found a significant correlation between clinical outcome and ASD [13]. In a 30-year follow-up comparing patients undergoing various spinal procedures (fusion, discectomy, decompression), Kumar et al. [14] found that the incidence of radiographic changes in levels above the operated region was twice as high after fusion as after the other procedures. In contrast, validated scales and functional testing (e.g. SF-36) showed no significant differences in outcome. The author concluded that radiographic changes do not necessarily lead to functional impairment in all patients following lumbar spine fusion for degenerative disc disease. There is other evidence suggesting that radiologic degeneration of the superior adjacent segment does not correlate with clinical results [15]. In a cohort of 215 patients after lumbar spine arthrodesis, Ghiselli et al. reported an adjacent segment disease rate of 16.5% after 5 years. This rate increased to 30.1% at ten-year follow-up [16]. However, a previous review suggests that there may be a correlation between fusion and the development of adjacent segment degeneration when compared to arthroplasty. This correlation appears even stronger when observing adjacent segment disease, thus underscoring the impact of fusion procedures on adjacent segments [3].

### Objective

Do topping off devices lead to better or at least equivalent clinical outcomes compared to standard fusion? Does topping off prevent development of adjacent instability? Does radiographic ASD correlate with clinical outcome? Does topping off lead to a higher complication rate (e.g., implant failure) than regular fusion?

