### Sample size

Our target recruitment is 30 patients. We assume a loss of follow-up of 10%, so that 27 patients should be available for the final analysis. The normalized form of the SF-36™ PCS (mean 50, standard deviation 10) is assumed. With this number of patients, using a two-sided t-test, a normalized PCS score difference of 11.2 or more could be detected with a power of 80% and alpha = 0.05.

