### Data analysis

The PCS and MCS sub-scores and the ODI score are measured repeatedly; thus, areas under the curve (AUC) will be computed. AUCs will be compared between treatment groups using a two-sample t-test.

Time until ASD or adjacent segment instability will be analyzed using the life-table method and compared between treatment groups using the log-rank test.

The primary analysis set is defined according to the intention-to-treat principle, including all randomized patients and interpolating missing longitudinal data. Robustness of results will be investigated by additional analyses based on the per-protocol set. Interim analyses are not foreseen.

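### The first objective includes an at-least-equivalent question, but the sample size and every named test address only a difference, with no margin or confidence-limit rule

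*Protocol article*

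**What the plan says.** In the protocol article, the Objective section opens with the question "Do topping off devices lead to better or at least equivalent clinical outcomes compared to standard fusion".

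The Sample size section is written wholly in terms of detecting a difference. It states "Our target recruitment is 30 patients" and "We assume a loss of follow-up of 10%, so that 27 patients should be available for the final analysis". On variability it says "The normalized form of the SF-36™ PCS (mean 50, standard deviation 10) is assumed", and it concludes that, "using a two-sided t-test, a normalized PCS score difference of 11.2 or more could be detected with a power of 80% and alpha = 0.05".

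The Data analysis section forms areas under the curve for PCS, MCS and ODI, and says "AUCs will be compared between treatment groups using a two-sample t-test". Time to ASD or adjacent segment instability is "compared between treatment groups using the log-rank test". The primary set is all randomised patients with missing longitudinal values interpolated. A per-protocol analysis serves as a robustness check.

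The article states no equivalence or non-inferiority margin, no one-sided or two one-sided test, and no rule based on a confidence limit. It does not say how a non-significant result will be interpreted.

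**The concern.** A claim that a treatment is at least equivalent needs evidence that any deficit is smaller than a stated amount. A two-sided test of no difference does not supply that: failing to reject is compatible with equality, with benefit and with material harm. The objective therefore asks something that neither the sizing nor the named tests can answer.

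The point matters because a non-significant result is likely unless the true effect is large. The Background section reports that an earlier randomised trial of 60 patients, twice this size, found no clinical difference and a higher rate of implant failure with the hybrid device. If the same happens here, the wording of the objective leaves room to report it as met while a deficit of more than half a standard deviation is still compatible with the data.

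**Working it through.** **Inputs from the article.** 30 recruited, 10% loss, 27 analysed; SD 10; two-sided alpha 0.05; power 80% (Sample size). Two arms kept in balance by blocking (Randomization). The allocation ratio is not given as a number, so 1:1 is assumed, that is 13 versus 14.

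**1. The plan's own figure.** 30 × 0.9 = 27. SE = 10 × √(1/13 + 1/14) = 3.85, with 25 degrees of freedom. By the noncentral t distribution, power at 11.2 points is 79.8%, and 80% power is reached at 11.23 points. The stated 11.2 reproduces.

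**2. How likely is a non-significant result?** Same distribution, SD 10, 13 versus 14:

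| True PCS difference | Probability of non-significance |
|---|---|
| 0 | 95% |
| 3 | 88% |
| 5 | 76% |
| 7.5 | 53% |
| 10 | 30% |

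**3. What could such a result exclude?** Half-width of the 95% interval = t(0.975; 25) × SE = 2.06 × 3.85 = 7.9 points. The chance that the lower limit lies above minus the margin, with truly equal arms, is the power of a one-sided 0.025 non-inferiority test. The margins are assumed, because the document gives none:

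| Margin (PCS points) | Chance of excluding that deficit |
|---|---|
| 3 | 11% |
| 5 | 24% |
| 8 | 51% |
| 10 | 70% |

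The chance reaches 80% only at a margin of about 11.2 points, more than one SD.

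**4. Closer to the planned analysis.** Steps 2 and 3 treat PCS as one score in 27 completers. The plan compares AUCs in all randomised patients and gives no SD for the AUC. Two adjustments:

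- *All 30 patients, SD 10.* SE = 10 × √(2/15) = 3.65; half-width = 2.05 × 3.65 = 7.5 points. This treats interpolated values as if they were observed.
- *Average over the five planned postoperative SF-36 assessments* (6 weeks; 6, 12, 24 and 36 months), assumed equally weighted with a common between-visit correlation ρ. SD of the average = 10 × √((1 + 4ρ)/5), which is 7.75 at ρ = 0.5 and 8.72 at ρ = 0.7. With 13 versus 14 the SE is 2.98 or 3.36, and the half-width 6.1 or 6.9 points.

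| Scenario | 95% half-width | Chance of excluding a 5-point deficit |
|---|---|---|
| Single score, 27 patients | 7.9 | 24% |
| Single score, 30 patients | 7.5 | 26% |
| Five-visit average, 27 patients, ρ = 0.7 | 6.9 | 30% |
| Five-visit average, 27 patients, ρ = 0.5 | 6.1 | 36% |

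Combining both adjustments at ρ = 0.5 gives 40% at 5 points. For the five-visit average in 27 patients, the margin that gives 80% power falls to 11.23 × 0.775 = 8.7 points (ρ = 0.5) or 11.23 × 0.872 = 9.8 points (ρ = 0.7).

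**The case against.** The strongest reply is that the Objective section lists four plain-language research questions, not statistical hypotheses. The tested hypothesis is clear from the Sample size and Data analysis sections, and the article nowhere calls itself an equivalence or non-inferiority trial. On that view the defect is loose wording in one sentence. That describes the scale of the repair fairly, but the clash remains: the first question asks for something that the sizing and the tests do not address.

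A second reply is that a journal article may leave interpretation rules to the full protocol or analysis plan. For reporting detail that is right. A margin, however, determines the sample size, and the Sample size section commits to detecting a difference. A margin set elsewhere would not change the question for which the trial was sized.

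Third, the figures for a single score do not describe the planned AUC analysis. This stands. They are approximations, and the AUC scenarios are somewhat more favourable. The probabilities of non-significance also partly restate that the trial is small, which is a separate matter.

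A reader might infer that a null result *will* be read as equivalence and used to support an expensive device with a larger surgical approach. The document does not support this. It never says how a null result will be read, and its stance is sceptical. The Background finds no convincing evidence of clinical benefit and notes that the earlier trial's authors advised against prophylactic use. The Discussion says nonessential use should be avoided because of cost and names the longer approach as a possible harm. Misreading is a risk that the objective leaves open, not a stated intention.

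**Conclusion.** The mismatch is real and lies between sections of the same article: the objective includes an at-least-equivalent question, while the sample size and all named tests concern a difference, with no margin or confidence-limit rule. That part of the objective cannot be concluded from the plan as written.

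Across the scenarios in 27 patients, a null result would carry a 95% interval of roughly ±6 to ±8 PCS points, and with truly equal arms a 5-point deficit would be excluded in about a quarter to just over a third of trials. These sizes rest on SD 10, 1:1 allocation, an illustrative margin and, for the AUC, assumed equal weights and correlations of 0.5 to 0.7. Other values would move the numbers but would not supply the missing margin.

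**What to change.** **Preferred.** Restate the first objective as a superiority question on PCS. State that a non-significant result will be reported as inconclusive, with its 95% confidence interval, and not as equivalence.

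**If the at-least-equivalent wording is kept.** Fix a justified margin now, on the scale of the planned AUC (for example, time-averaged PCS). Allow the claim only if the lower 95% confidence limit for the difference (topping off minus fusion) lies above minus that margin in the intention-to-treat analysis, with the per-protocol set as a consistency check. State the low power for it.

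**Cost.** Either option changes only wording and one decision rule, and needs no extra patients. The price is a narrower permitted claim. Powering the trial for non-inferiority would be a different undertaking. At an illustrative 5-point margin with SD 10 on a single score, 80% power and one-sided 0.025, the normal approximation gives 2 × (10 × (1.96 + 0.84)/5)² ≈ 63 per arm. That is 126 analysed, or 126/0.9 = 140 randomised.

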## Methods and Design

This study is designed as a randomized, parallel-group, therapy-controlled trial in a clinical care setting at a university hospital. Patients presenting to our outpatient clinic with degenerative disc disease or spondylolisthesis will be assessed against study inclusion and exclusion criteria. After informed consent and randomization of patients, surgery will be performed. Follow-up examinations will take place immediately after treatment during hospital stay, and then after another 6 and 24 weeks, for a total study duration of 6 months. Data will be assessed after 12, 24, and 36 months for a supplemental investigation. Further assessments will be performed annually, to account for the possibility that conclusions regarding ASD might not be definitive after 36 months.

Experimental research in this trial will be performed with the approval of the ethics committee of the medical faculty of the University of Cologne under the reference number 10-259. Research carried out in the trial will be in compliance with the Helsinki Declaration [17].

### Participants and recruitment

Patients over 30 years of age presenting to our outpatient clinic with degenerative disc disease or spondylolisthesis and indications for monosegmental lumbar spine fusion are eligible for trial inclusion. Surgery will not be considered until at least 6 months of conservative treatment have been concluded. Patients with spondylolisthesis must respond positively to facet joint injection. Radiologic inclusion criteria are summarized in the appendix.

Prerequisite to inclusion is the presence of radiologic degeneration of the adjacent segment (Pfirrmann grades II-IV in MRI findings [18]) without signs of instability. Definition of radiologic and clinical instability as well as further inclusion criteria are summarized in the appendix.

Study subjects will be approached and recruited by experienced spine surgeons. For the screening procedure, an estimated 150 patients per year will undergo primary monosegmental fusion within the department. Recruitment of approximately 30 patients per year is anticipated.

Patients participating in parallel interventional studies as well as patients with lumbar scoliosis (> 25° cobb angle), spondylolisthesis Meyerding IV, and/or radiologic ASD worse than Fujiwara grade II or Pfirrmann grade IV [18,19] are excluded from this study. Further exclusion criteria are summarized in the appendix.

### Interventions

▪ Patients will receive one of two treatments:

▪ Conventional monosegmental posterior lumbar intervertebral fusion (PLIF)

▪ Hybrid system (PLIF + flexible pedicle screw system above the fusion)

### Control group - conventional PLIF

The control group will receive a monosegmental posterior lumbar spine fusion with an intervertebral cage (PLIF). This is the current, well-established therapy for several pathologies of the lumbar spine (e.g. spondylolisthesis, degenerative disc disease). Thus, the control group will receive the standard of care. This is the only acceptable control/comparison in a trial of this kind. Surgery will be performed using the following devices: Optima ZS™ (Zimmer^® ^Spine Germany GmbH, Kiel, Germany), Wave^© ^Lumbar Cage (Advanced Medical Technologies AG, Nonnweiler, Germany)

### Intervention group - hybrid system

The intervention group will receive a hybrid system with PLIF and a flexible pedicle screw system above the fusion. Surgery will be performed using the following devices: Optima ZS™+ DTO™ (Zimmer^® ^Spine Germany GmbH, Kiel, Germany), Wave^© ^Lumbar Cage (Advanced Medical Technologies AG, Nonnweiler, Germany)

Only skilled spine surgeons (with minimum experience of 30 fusion procedures) will participate in the trial. Intraoperative photo documentation will assist in preventing variations of the procedure (e.g., enlargement of decompression/approach). We will also provide an instructional movie on the procedural standards as well as evaluation of the x-rays.

All patients will receive a surgical drain, to be removed 2 days post-surgery. Both groups of patients will receive physical therapy, beginning on the day after surgery. Patients will be discharged only after sufficient convalescence with unremarkable wound healing. Hospital admission lasting 8-10 days will be necessary. Physical therapy will be performed during the inpatient period. After hospital discharge, physical therapy will be continued under outpatient conditions. This therapy will not be standardized in order to reflect reality.

### Outcome measures and assessments

#### Primary Outcome Measures

The focus of this investigation is on subjective and objective clinical benefits for the patient. Functional outcomes will be evaluated using the SF-36™ score after 6 weeks as well as 6, 12, 24, and 36 months after surgery. The SF-36™ is the most frequently used generic health status measure worldwide. In the past, spine surgery investigations have focused on technical outcomes; however, more recently they have turned to clinical results [20,21]. It is unclear whether radiologic parameters correlate with clinical success; thus, they are poor measures of primary outcome. Recent, important randomly controlled trials (RCTs) in spine surgery have used the SF-36™ and ODI tools to assess clinical outcomes [22,23]. Parameters like pain and walking distance are represented in the SF-36. The development of physical (PCS) and mental health (MCS) component scores has eased interpretation and cross-cultural comparison of the SF-36™. The SF-36™ is a standardized questionnaire to detect patient quality of life corresponding to conditions of health. It yields an 8-scale profile of functional health and well-being scores, as well as psychometrically-based physical and mental health summary measures, and a preference-based health utility index. Thus, the SF-36™ and the patient responses contained within are a good measure of primary endpoint. Points are awarded for individual answers by each patient and added to yield a sum total. The SF-36™ PCS scores of the experimental and control groups will be compared to further quantify patient outcome. Subsequent follow-up will repeat the SF-36™ to ensure assessment for clinical impairment and/or the manifestation of a clinical or radiologic instability. This follow-up will continue for up to 3 years and further after treatment. In cases of impairment, x-ray is medically indicated at any point of time.

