#### Secondary Outcome Measures

1. Total, MCS, and 8 individual dimensions and subscales of the SF-36™ (version 4.0) for confirmation and clarification of the primary outcome results.

2. ODI (cross-cultural adaption of the ODI version 2.1 for use with German-speaking patients)[24]: this is one of the condition-specific questionnaires recommended for use with back pain patients. The ODI is a standardized, patient-completed questionnaire which gives a subjective percentage score of level of function (disability) in activities of daily living for those rehabilitating from low back pain. The questionnaire examines perceived level of disability in 10 everyday activities of daily living.

3. COMI questionnaire (version 2008): a patient-oriented, short, multidimensional outcome instrument validated for patients with spinal disorders.

4. X-rays will be taken after 6 weeks, 6, 12, 24, and 36 months. Further assessments will be performed annually. These are common intervals after surgical implant procedures not requiring extraneous radiation. At the point in time where adjacent instability is identified radiographically, we will reevaluate and compare the clinical outcome. Criteria for radiologic ASD as well as adjacent instability are listed in the appendix (definition of radiologic instability and Weiner's classification). Pre- and postoperative x-rays must be compared to assess the Weiner's classification score. X-rays will be evaluated by experienced radiologists.

5. Clinical ASD will be assessed (see appendix for the definition).

6. Work-related function/disability at the time of surgery and after surgery, plus the duration until return to work. At each visit, patients will be interviewed about their level of work-related function/disability as well as the time point when/if they return to employment.

7. Inpatient mortality and mortality at 6 months.

8. Surgery-related data (blood loss, length of incision, duration of surgery) are taken from the surgical report.

9. Intraoperative and postoperative complication rates (e.g. implant failure)

10. Adverse events (AE) and serious adverse events (SAE) will be documented and monitored throughout the study.

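### Comparing clinical outcome at the moment instability is seen on film can create a link with symptoms if films taken because of impairment count

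*Protocol article*

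**What the plan says.** Item 4 of Secondary Outcome Measures sets the film schedule: "X-rays will be taken after 6 weeks, 6, 12, 24, and 36 months". It continues: "Further assessments will be performed annually". The same item fixes when clinical status is looked at in relation to the film: "At the point in time where adjacent instability is identified radiographically, we will reevaluate and compare the clinical outcome".

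Primary Outcome Measures describes the repeated questionnaire as part of the search for instability: "Subsequent follow-up will repeat the SF-36™ to ensure assessment for clinical impairment and/or the manifestation of a clinical or radiologic instability". The next statements extend this follow-up to three years and beyond and then add: "In cases of impairment, x-ray is medically indicated at any point of time".

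Two aims depend on these films. The third question under Objective is: "Does radiographic ASD correlate with clinical outcome". For the between-arm question, Data analysis says: "Time until ASD or adjacent segment instability will be analyzed using the life-table method and compared between treatment groups using the log-rank test". The article does not say whether a film taken because of impairment can supply an event for either aim.

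**The concern.** Between scheduled visits, whether a patient is filmed depends on how the patient feels. The at-detection rule then reads the clinical outcome at the time of that film. If the film shows instability, the clinical score attached to it is poor because impairment was the reason for the film. A well patient with the same change is found at the next fixed visit, which after month 12 can be 12 months later.

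The film finding is therefore ascertained conditionally on the outcome it is to be related to. The Background and Primary Outcome Measures sections both treat the link between radiologic change and symptoms as unsettled, so an answer produced partly by the timing of films would mislead on one of the four stated questions. There are two lesser routes. Extra films give impaired patients more chances of a false positive on one of the seven instability criteria in the Appendix. They also bring detection dates forward, which matters for the comparison of arms if one arm has more impairment.

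**Working it through.** **What is not touched.** The article's own figure reproduces. With 27 patients (30 × 0.9, split 13 and 14), SD 10, two-sided alpha 0.05 and the noncentral t distribution, a PCS difference of 11.2 has 79.8% power. The detectable difference at 80% power is 11.23. Neither depends on films.

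**Inputs.** From the article: films at 1.5, 6, 12, 24 and 36 months; ASD incidence of up to 24% at an average of 39 months (Background), used here as 24% over 36 months. Assumed, because the article gives no figures: 0.25 to 1 impairment episode per patient-year, each lasting 1.5 or 3 months, with one film at its start; 0 or 3% false positives per film; ASD incidence of 10% as a second scenario; onset spread evenly over 36 months and independent of impairment. The true association is therefore nil.

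**Step 1: how much ASD is first seen on a triggered film.** For an onset in a gap of g months with episode rate λ per month, the chance that a triggered film precedes the next visit is 1 − (1 − e^(−λg))/(λg). At 0.5 episodes per year, λ = 0.5/12.

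| Gap (months) | Number of gaps | Chance of triggered detection |
|---|---|---|
| 12 | 2 | 0.213 |
| 6 | 1 | 0.115 |
| 4.5 | 1 | 0.088 |
| 1.5 (before the first film) | 1 | taken as 0 |

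The weighted share is (24 × 0.213 + 6 × 0.115 + 4.5 × 0.088)/36 = 0.17. The simulation gives the same 17%, and 9% to 34% over all scenarios.

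**Step 2: clinical state at detection.** In the scenario with 24% incidence, 0.5 episodes per year, 3-month episodes and no false positives, the background share impaired at a visit is 1 − e^(−0.5 × 0.25) = 11.7%. Patients found on triggered films are all impaired. Those found at scheduled visits are impaired in only about 2.6%, because most impaired cases have already been found. Overall, 0.17 × 1 + 0.83 × 0.026 ≈ 19% (simulated: 19.1%). The odds ratio against background is (0.191/0.809)/(0.117/0.883) = 1.78, with no true link.

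| Films counted | Odds ratio, impaired at detection v background, all scenarios |
|---|---|
| Scheduled only | 0.91 to 1.04 |
| Scheduled plus triggered | 1.75 to 4.95 |

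The comparator is the share impaired at the visits from 6 to 36 months. This is a choice made here, since the article names none.

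**Step 3: ASD at any time by 36 months.** If the change is progressive and read without error, the fixed films find it in everyone by 36 months, and the odds ratio stays at about 1.0. Only the mean detection lag falls. With scheduled films it is (1.5² + 4.5² + 6² + 12² + 12²)/(2 × 36) = 4.8 months. With 1 to 2 extra films per year in impaired patients it is 2.8 to 3.6 months.

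False positives change this. Assume an error rate f per film, independent between films, and 3 extra films (8 instead of 5). With 24% true ASD in both groups, the share labelled as ASD is 0.24 + 0.76 × [1 − (1 − f)^n].

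| f | 5 films | 8 films | Risk ratio |
|---|---|---|---|
| 2% | 0.24 + 0.76 × 0.096 = 31.3% | 0.24 + 0.76 × 0.149 = 35.3% | 1.13 |
| 5% | 0.24 + 0.76 × 0.226 = 41.2% | 0.24 + 0.76 × 0.337 = 49.6% | 1.20 |

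If 30% of the 27 analysed patients are impaired (assumed), that is 8.1 patients. The excess is 8.1 × 0.040 = 0.3 to 8.1 × 0.084 = 0.7 falsely labelled patients.

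**Step 4: the log-rank test.** Film frequency can distort it only if impairment differs by arm. Even then, with life-table intervals that follow the visits, films at 18 and at 24 months fall in the same interval and no date moves. The shift of up to 12 months arises only if exact detection dates are used.

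**The case against.** The strongest reply is that the triggered film is a matter of care, that the radiologic outcome is defined by the scheduled films, and that a condensed article may leave to a fuller document which films count. This stands in part: nothing in the article says a triggered film is an event, and the point is conditional on that. But the at-detection comparison is stated, not omitted, and a fuller plan would have to replace it as well as restrict the films. It is also fair that the article does not say with whom the outcome at detection is compared, or that this comparison is the analysis of the correlation question. The risk lies in using it that way.

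A reader might infer three stronger things, and the article supports none of them:

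- That the correlation question must come out positive whatever the truth. It need not. All patients have the fixed films, and ever having ASD by 36 months is essentially unbiased for progressive change read without error.
- That impaired patients have about 1.5 times the risk of a false ASD label overall. The ratios 0.149/0.096 = 1.55 and 0.337/0.226 = 1.49 hold only if nobody truly has ASD. At 24% incidence they fall to 1.13 and 1.20.
- That the comparison of arms is biased. The Discussion says only that the longer approach could worsen outcome. It gives no difference in late impairment or in film counts.

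**Conclusion.** The point holds for the comparison of clinical outcome at the moment of detection, provided that triggered films count, which the article neither states nor excludes. Under no true association that comparison gave odds ratios of 1.75 to 4.95. The range depends on assumed episode rates, episode lengths and film error, so it shows direction and plausible size and is not a forecast. The effect on ever having ASD by 36 months is small (risk ratio about 1.1 to 1.2) and rests on assumed error rates and film numbers; only the 24% comes from the article. The effect on the log-rank test needs both unequal impairment between arms and exact event dates. The primary PCS comparison and the sample size stand. This is an inexpensive improvement to a secondary question and does not threaten the trial's main result.

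**What to change.** Leave clinically indicated films as they are; only the analysis changes.

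- For the correlation question, compare PCS and ODI between patients with and without radiologic ASD at the same scheduled visit, for example 36 months, instead of at detection.
- For time to ASD or instability, assess the radiologic component on scheduled films and set the life-table intervals to the scheduled visits. List findings from unscheduled films separately.
- If a patient has further surgery on that segment, or is lost, before the next scheduled film, count instability seen on an unscheduled film as an event in that visit interval. Without this rule, true events would drop out mainly among impaired patients and could bias the result the other way.
- Give a sensitivity analysis that includes all films.

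The cost is a few sentences in the outcome and analysis sections, coarser event dating and one extra sensitivity analysis. No extra films are needed.
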